### Procedure for unblinding if needed {17b}

It is an open-label study and therefore unblinding will not occur.

## Data collection and management

### Plans for assessment and collection of outcomes {18a}

During the online registration, contact data of all interested individuals will be collected. The data will be deleted if the person disagrees to participate in the trial.

All parameters as described in the subsection “Outcomes (see {12})” will be taken in a group testing setting with appropriate Coronavirus SARS-CoV-2 (COVID-19) safety measures, e.g., testing, vaccination, hygiene procedures by the staff of the St. Pölten University of Applied Sciences either at the university itself or at the Landesklinikum Wr. Neustadt, Hollabrunn, or Mauer/Amstetten.

The measurements will take place in the morning in a fasting state and with anthropometric measurements with light clothing. Anthropometric measurements will be conducted by dietitians. Blood pressure and blood samples will be taken by nurses. Fresh blood samples will be taken by the staff of the St. Pölten University of Applied Sciences, centrifuged within a timeframe of twenty minutes, and analyzed within a timeframe of 3 h maximum after the centrifugation by the University Hospital St. Pölten. The laboratory of the University Hospital St. Pölten is ISO 9001-certified and will handle all samples according to its quality management.

### Plans to promote participant retention and complete follow-up {18b}

To minimize loss during the follow-up, and in order to promote participation in the follow-up measurements, the same strategy is implemented as for compliance with the intervention measurements (see {11c}): as convenient as possible, reminders 48 h ahead of the measurement, possibility to discuss the measurements’ results with the dietitian, and a financial compensation paid after the last measurement.

During the follow-up, participants of the intervention group can use the instant messaging service and continue their communication with the group members and the moderator, hence, without support of the study team. The moderator will be instructed to motivate the group members to participate in the follow-up measurement. The relationship of trust and social support in the groups as well as with the study staff will support a higher degree of complete follow-up.

### Data management {19}

The participants agree that for the purpose and in the course of this study, the St. Pölten University of Applied Sciences will collect and process the following personal data: name, age, gender, education, income, occupational situation, housing situation, migration background, personality characteristics, clinical information such as age at diabetes diagnosis, social support, self-efficacy, depression, quality of life, diabetes knowledge, treatment adherence, diet and exercise behavior, nicotine and alcohol consumption, diabetes self-management, medical consultations during the last 6 months, HbA_1c_, fasting glucose, total cholesterol, HDL, LDL, triglycerides, blood pressure, body weight and height, waist circumference, and body composition.

Furthermore, the participants agree that the University Hospital St. Pölten may transmit the following data in indirectly personalized (pseudonymized or encrypted) form to the St. Pölten University of Applied Sciences for the purpose of analyzing whether the intervention is effective with regard to the defined parameters compared to conventional therapy: HbA_1c_, fasting glucose, total cholesterol, HDL, LDL, triglycerides.

The participants’ data will be pseudonymized and assigned a fixed identification code. This code will be stored safely in a password-protected file, accessible only by the study coordinator (EH) and central staff members (UH, AEZ). The key for the coding is kept separately and inaccessibly by the study coordinator. Thus, it is only possible for persons who are entrusted with the evaluation of the data to infer the identity of the participants.

Data acquisition and data processing are performed using commercial software. All data obtained are stored in computer files in encrypted form. The coding is done by means of consecutive numbering, from which only the allocation to the corresponding group, but in no case a conclusion as to the identity of the participant is possible.

Data will be stored and analyzed via the statistical software package SPSS at servers of the St. Pölten University of Applied Sciences, only used for this special study and not be passed on to third parties. The handling of the data complies with the European General Data Protection Regulation, the Austrian Data Protection Act, and the recommendations of the Ethics Committee of Lower Austria.

To be able to merge the data from the paper-and-pencil questionnaires, anthropometric measurements, and blood pressure data, a defined coding system will be used. Therefore, the study coordinator will take part in every measurement and organize the participants and coding system. Hence, every participant will get his or her identification code and the questionnaires will be marked with this code at the beginning of each measurement. The identification code ensures that the study staff do not know to which group each participant belongs. Paper-and-pencil questionnaires will be checked by the study staff in terms of completeness and correctness related to the specifications of the questionnaires. These data will be transferred into SPSS manually and controlled by another member of the study team. Results of the biochemical analysis will be mailed via encrypted Excel files from the University Hospital St. Pölten to the St. Pölten University of Applied Sciences and imported into SPSS by the study coordinator. Blood samples will be disposed of and Excel files will be deleted after integration into SPSS. Furthermore, the St. Pölten University of Applied Sciences performs data back-ups on a daily basis. All signed informed consent forms as well as all collected paper-and-pencil sheets will be stored in a locked place, accessible only to the study coordinator and a central staff member (UH). All data will be stored at the St. Pölten University of Applied Sciences for ten years after the study’s end. After that, all data will be destroyed.

To ensure data quality, the study coordinator will control the data regularly including checking the range of values or double data entry.

Data protection concerning the instant messaging tool will be met by using the instant messaging communication tool *mattermost* (https://mattermost.com/). *mattermost* has been chosen for its clear terms and conditions and data handling strategy. The open-source software *mattermost* was chosen because it can be operated securely and privately, as we will run it on-premise and not as a cloud solution. *mattermost* will be hosted as a software solution in an ISO 27001:2013 certified data center in Vienna for the duration of the project. *mattermost* provides a holistic messaging solution that allows to communicate securely and efficiently via 1:1 and group messaging, meeting, and file sharing as well as audio/video integrations. The data export based on Docker is conducted in the Viennese data center and made available only to selected members of the study team (EH, AEZ, JG). The data are cleaned, and unstructured communication data will be structured using content analysis and MAXQDA (see {12}). Subsequently, these data will be pseudonymized and transferred into SPSS for further analysis.

Results of all analyses will be reported in an aggregated and strictly anonymous form.

### Confidentiality {27}

All collected data will be kept confidential as described in “Data management” (see {19}). Only the study coordinator and central staff members (UH, AEZ) can open the password-protected file to link personal information and code. The final pseudonymized dataset in SPSS will be used by the study staff for analyses, publications, and reports only for this study.

### Plans for collection, laboratory evaluation, and storage of biological specimens for genetic or molecular analysis in this trial/future use {33}

Not applicable as no biological specimens for genetic or molecular analysis will be collected.

## Statistical methods

### Statistical methods for primary and secondary outcomes {20a}

Data will be analyzed using IBM SPSS Statistics 26 or greater (IMB Corporation, Armonk, NY, USA). The significance level will be set at 5%. Generally, metric data will be checked for normal distribution using a histogram of each variable, as well as for skewness and kurtosis. To illustrate descriptive parameters, the arithmetic mean and the 95% confidence interval will be stated for metric data. Interval variables or nominal scaled variables will be shown as frequencies. Repeated measures ANCOVA will be used to compare the control and intervention groups concerning primary and secondary outcome parameters. Non-normal metric data will be analyzed using the Mann-Whitney *U* test, the Kruskal-Wallis signed rank test, or the Friedman-Test [73].

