### Trial design {8}

The presented trial is a parallel-group, two-arm superiority RCT to evaluate the efficacy of a peer-supported IMS intervention for patients with type 2 diabetes mellitus in Lower Austria. Peer support via IMS in addition to standard therapy is compared with stand-alone standard therapy.

Moderators play a central role in peer-supported IMS intervention because they initiate and moderate the IMS exchange and discussion. They are patients with several years of disease and therapy experience because they need personal and practical experience in order to provide supportive and credible coaching. All moderators receive prior training and guiding material (see {11a}). The moderators are supported by a dietitian at regular intervals and by other study team members if needed. One moderator is responsible for one IMS group consisting of 14 participants maximum.

The participants will be fully informed about all aspects of the trial and asked to sign a consent form. The participants will be randomized at a ratio of 1:1.

The duration of the intervention is 7 months, followed by a 7-month follow-up period. The intervention will be performed twice to expand the recruitment phase. During the follow-up, the intervention group is expected to use the IMS tool without guidance by health professionals and both groups receive standard therapy.

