### Sample size {14}

An a priori calculation was performed using G-Power [68] for the primary outcome variable HbA_1c_, using an ANCOVA at 5% level of significance and 80% power. Based on previous research, we assumed a small to medium effect size for group differences in HbA_1c_ means (partial eta squared = 0.05, which corresponds to an effect size *f* = 0.229) [69–71]. Considering a 30% dropout ratio, we will include 98 randomly assigned participants in each group (196 total). The intervention group will be subdivided into seven IMS groups made up of 14 participants and one moderator each. Therefore, nine moderators (seven plus two for the compensation of possible drop-outs) will be additionally recruited (205 persons in total, 196 participants plus nine moderators). Although the moderators will participate in the assessments, their data will not be included in the analyses.

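### The fallback for non-normal data is triggered by the raw distribution of HbA1c and can replace the planned arm comparison with tests that take no covariate or do not compare the arms

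*Protocol article*

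**What the plan says.** All of the relevant text is in the section Statistical methods for primary and secondary outcomes {20a}. It sets out three steps.

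- A check: "metric data will be checked for normal distribution using a histogram of each variable, as well as for skewness and kurtosis". No cut-off is given, and model residuals are not mentioned.
- A main analysis: "Repeated measures ANCOVA will be used to compare the control and intervention groups concerning primary and secondary outcome parameters". No covariate is named.
- A replacement: "Non-normal metric data will be analyzed using the Mann-Whitney" U test, "the Kruskal-Wallis signed rank test, or the Friedman-Test". Nothing says which of these answers which question, and no outcome is exempted.

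Outcomes {12} defines the primary outcome as the HbA1c level in per cent, measured at four visits (T0 to T3). It is metric, so the replacement sentence covers it. Trial design {8} describes a "parallel-group, two-arm superiority RCT". Sample size {14} rests on ANCOVA alone, "using an ANCOVA at 5% level of significance and 80% power", with "partial eta squared = 0.05, which corresponds to an effect size" f = 0.229.

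**The concern.** The replacement is a stated rule, so this is not a case of detail left to a later document. Read literally, a skewed HbA1c histogram moves the primary comparison off the model on which the trial was sized, even if that model's residuals are well behaved. It moves to a list in which one test has no arm factor and one cannot be identified by name.

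Two things are at stake. First, the primary test is settled only after the outcome distribution has been seen, with no threshold and no order of preference among the substitutes. Second, the new test may be less powerful or may answer a different question from H1, which is a comparison between arms.

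**Working it through.** **1. What each listed test can do for H1.**

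- Mann-Whitney compares two arms, takes no covariate and uses one value per person. The four visits are not used jointly.
- Kruskal-Wallis compares independent groups and, with two arms, is equivalent to Mann-Whitney. Signed rank is a paired, within-group test. A test carrying both names does not exist, so the text does not determine what would be run.
- Friedman compares time points within subjects and has no arm factor. As an illustration, I simulated one arm of 69 people with four visits, no treatment effect and an assumed within-person correlation of 0.6. A common shift after baseline of 0.1, 0.2 or 0.3 SD made Friedman reject in about 10%, 35% and 70% of trials. It responds to any shared trend.

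**2. The plan's own sample size.** Partial eta squared 0.05 gives f = √(0.05/0.95) = 0.229, as stated. Noncentral F power for ANCOVA (numerator df 1, two groups, λ = f²N, α = 0.05) reaches 80% at N = 152. Inflating by 1.3 gives 152 × 1.3 = 197.6, close to the planned 196. With 30% loss, 196 × 0.7 = 137 complete, and ANCOVA power at 137 is about 76%. That is the reference below. The gap between 76% and 80% comes from the dropout allowance, not from the fallback.

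**3. Power after a switch to Mann-Whitney.** On the residual scale d = 2f, about 0.459 from f = 0.2294. With an assumed correlation r between baseline and outcome:

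- post value: d = 0.459 × √(1 − r²), which is 0.398, 0.367, 0.328 and 0.275 at r = 0.5, 0.6, 0.7 and 0.8;
- change from baseline: d = 0.459 × √[(1 − r²) / (2(1 − r))], which is 0.411 at r = 0.6 and 0.423 at r = 0.7.

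The normal-data rows use 68.5 per arm and Mann-Whitney efficiency 0.955. The skewed rows are simulated.

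| Situation | Assumed r | ANCOVA | Mann-Whitney |
|---|---|---|---|
| Normal data, post value | 0.5 / 0.7 / 0.8 | about 76% | 62% / 46% / 35% |
| Normal data, change from baseline | 0.6 / 0.7 | about 76% | 65% / 68% |
| Skewed baseline, normal residuals, post value | 0.5 / 0.7 | 74–76% | 64% / 50% |
| Strongly skewed residuals too, post value | 0.5 / 0.7 | about 76% | 82% / 63% |

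The third row is the case in which a check on raw variables switches needlessly. There ANCOVA keeps a type I error of 4–5%.

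**4. How likely the switch is.** The document gives no HbA1c mean or SD. I assumed a source mean of 7.0 to 7.5%, SD 1.0 to 1.3 and n = 196, and flagged a sample when a 5% skewness test rejected.

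- Normal source, cut at 6.5% exactly at T0: skewness 0.6 to 0.8, flagged in 94–100% of samples.
- Normal source, cut on an earlier value correlated 0.6 to 0.8 with T0: skewness 0.1 to 0.3, flagged in 6–32%.
- Source already right-skewed: skewness 1.3 to 2.4, flagged in about 100%.

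The flagging rule matters as much. If only absolute skewness above 1 counts, the first case falls to 1–16% and the second to zero.

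**The case against.** A reader might infer that the entry criterion of HbA1c at or above 6.5% truncates the outcome and so makes the switch likely. The document does not support this. Eligibility criteria {10} applies the limit to the most recent measurement before the trial, not to T0 and not to the later visits at which the arms are compared. Values below 6.5% at T0 are possible, no threshold for non-normality is set, and the judgement is partly visual. If the source population is already skewed, the entry criterion is not the cause.

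A reader might also infer that the switch gives up a baseline adjustment the plan has specified, at a fixed cost in power. The plan says ANCOVA but names no covariate, so baseline adjustment is the natural reading, not a stated fact. The largest losses assume normal data, where the switch should not fire, and Mann-Whitney on the raw post value, which the text does not specify. On change scores the loss is smaller, and with strongly skewed residuals the rank test can win.

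Finally, the text ties the arm comparison to the ANCOVA and never says that Friedman will compare arms. Reporting within-arm change as a treatment effect is therefore a possibility the wording leaves open, not something the plan announces. Which test serves which question could be left to an analysis plan.

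These objections remove any claim of a likely trigger or a certain power loss. They do not rescue a rule that covers the primary outcome, checks the wrong quantity, includes a test that cannot be identified and lists another that cannot address H1.

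**Conclusion.** The point holds as a defect in a stated rule. The analysis of HbA1c is made to depend on its raw distribution instead of model residuals. If HbA1c is judged non-normal, the named substitutes drop any covariate and the joint use of the visits, cannot be identified, or do not compare the arms. This much follows from the text without numerical assumptions.

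The probability of a switch cannot be determined from the document; it runs from about 6% to about 100% across the settings tried with the 5% skewness test. The effect on power, against about 76% for ANCOVA at 137 completers, runs from a drop to about 35% to a gain to about 82%. It depends on the baseline correlation, the shape of the residuals and whether post values or changes are ranked, all of which are assumed here. The effect of choosing the test after seeing the data on the 5% level was not quantified.

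**What to change.** In Statistical methods for primary and secondary outcomes {20a}:

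- For HbA1c, keep the covariate-adjusted between-arm repeated-measures model as the primary analysis whatever the raw histogram shows, and name baseline HbA1c as the covariate.
- Check model residuals instead of raw variables.
- Name one sensitivity analysis in advance and run it regardless of the check, for example log-transformed HbA1c, or the same model with bootstrap or robust standard errors. A list to choose from after seeing the residuals would bring the problem back.
- Remove Friedman and signed rank as between-arm tests and correct the Kruskal-Wallis name. If within-arm change over time is to be described, say so separately.

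The cost is a few sentences and a little extra analysis. The sample size and the data collected do not change. It is best settled before outcome data are examined by arm.

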### Interim analyses {21b}

There will be no planned interim analysis or stopping guidelines for medical reasons besides the exclusion criteria (see {10}) because no potentially harmful outcomes are expected based on the peer-supported IMS intervention. Nevertheless, participants can be excluded from the intervention group if they do not follow the rules of interaction set and agreed upon in the IMS group (see {11b}).

### Methods for additional analyses (e.g., subgroup analyses) {20b}

As we want to assess the association between specific personality traits and the benefits of peer-supported IMS, we use validated and published questionnaires, which we repeatedly distribute to all experimental and control groups at different times of the study.

In addition to the observed communication behavior, we use the information from the questionnaires (see {12}) to test the hypotheses and in particular related to (H2) diabetes self-management behaviors, (H3) quality of life of participants, and (H4) medication adherence as well as (H5) the level of extraversion.

### Methods in analysis to handle protocol non-adherence and any statistical methods to handle missing data {20c}

All participants’ data will be analyzed following the intention-to-treat principle. Scores for scales with at least 80% of items responded will be analyzed. For these cases, the nearest neighbor method will be used to replace missing data points. Furthermore, we will check the randomness of missing data by calculating the MCAR (missing completely at random) classification.

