Additionally, clinical visits will be designed as conveniently for the participants as possible [50, 51]. The participants will have easy access to the locations of training sessions and measurements: they can choose one out of four central locations in Lower Austria for their measurements. These locations are well known and easily accessible: the St. Pölten University of Applied Sciences and hospitals in Wr. Neustadt, Hollabrunn, and Mauer/Amstetten. These locations are equally distributed over Lower Austria from a geographical point of view and can be reached comfortably by car as well as public transport. The training sessions for the participants will take place after the first measurement at the same location. The training sessions for the moderators will be held at the St. Pölten University of Applied Sciences. Therefore, only individuals from St. Pölten or the surrounding areas are eligible to become moderators. If a participant misses one measurement, it is possible to make a new appointment within a certain timeframe.

Furthermore, study staff will call participants to schedule visits and send them reminders via SMS and e-mail 48 h before the appointment. During each measurement, participants and moderators will have the opportunity to discuss their results, such as body composition, with an experienced dietitian, which is not very common in Austria and will increase engagement [50].

Additionally, participants and moderators will receive a financial compensation of 50 EUR and a small gift after the last measurement.

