### Outcomes {12}

Data will be collected four times over a period of 14 months: at baseline (T0), 3 months after the start of the intervention (T1; T0+ 3 months), at the end of the intervention (T2; T0+ 7 months), and after the follow-up (T3; T0+ 14 months), including the following collection of biochemical, psychosocial, and behavioral parameters during all four data collection points.

The primary outcome is the level of HbA_1c_ [%] measured using TOSOH G8 (Sysmex Austria GmbH).

Secondary outcomes are:

Psychosocial parameters:

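### Repeated measures ANCOVA in its standard SPSS form drops anyone with a missed visit, and no stated rule restores them, so the intention-to-treat promise for HbA1c is not met as written

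*Protocol article*

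**What the plan says.** Section {20c} commits to intention to treat for all participants: "data will be analyzed following the intention-to-treat principle". Its missing-data rule has two parts. First, "Scores for scales with at least 80% of items responded will be analyzed". Then, "For these cases, the nearest neighbor method will be used to replace missing data points". It adds a check of whether data are missing completely at random, with no stated consequence.

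Section {20a} fixes the software, "Data will be analyzed using IBM SPSS Statistics 26 or greater", and the model: "Repeated measures ANCOVA will be used to compare the control and intervention groups concerning primary and secondary outcome parameters". For non-normal data it lists rank tests, the Friedman test among them. It does not list the visits that enter the model, the covariates or the estimation method.

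Section {12} sets the visits: "Data will be collected four times over a period of 14 months", at T0, T1 (3 months), T2 (7 months) and T3 (14 months). Section {14} allows for 30% dropout and randomises 98 per arm, 196 in total.

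On missed visits, section {11c} says: "If a participant misses one measurement, it is possible to make a new appointment within a certain timeframe". On retention, section {18b} applies the strategy of {11c} to the follow-up and adds for the intervention groups: "The moderator will be instructed to motivate the group members to participate in the follow-up measurement".

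**The concern.** The named model and the stated missing-data rule do not fit the stated analysis population. Intention to treat compares everyone as randomised. Repeated measures ANCOVA, run in the usual SPSS way, compares only those with a value at every modelled visit.

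Two things are at stake. First, those who stay to month 14 may differ between the arms in ways randomisation no longer balances. Participants know their allocation, and only one arm has a moderator encouraging attendance at T3. Second, HbA1c values that were measured at T1 and T2 are discarded because a later value is absent.

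**Working it through.** **Inputs.** From {14}: 196 randomised, 98 per arm, 30% dropout, partial eta squared 0.05, 5% level, 80% power. From {12}: four visits. From {20a} and {20c}: the model, the software and the item-level rule. The missed-visit rates and the timing of dropout below are my assumptions and are marked as such.

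**1. The plan's own figure.** f = √(0.05/0.95) = 0.229. With a noncentral F test (1 numerator df, λ = N·f²), 80% power needs N = 152; N = 151 gives 79.98%. Multiplying by 1.3 gives 151 × 1.3 = 196.3 or 152 × 1.3 = 197.6, close to the stated 196. So 196 is consistent with a requirement of about 151 plus 30%, although a repeated-measures calculation with an unreported correlation could also reach it. Whether the allowance should have been a division by 0.70 is a separate sample-size question.

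**2. What happens to a participant who misses T3.**
- Model: the standard SPSS general linear model for repeated measures deletes listwise, so the participant leaves the analysis if T3 is modelled.
- Item rule: it applies to scales with at least 80% of items answered. A missed visit has no items answered, and HbA1c is a laboratory value with no items. The rule does not apply.
- Rebooking under {11c}: this may prevent some missed visits, but it says nothing about analysing those that remain.
- Check for missing completely at random: it may describe the problem but does not bring the participant back.
- Friedman test as fallback: it also needs complete blocks.

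Nothing in the article keeps this participant in the HbA1c analysis.

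**3. Size at the planned dropout.** Lost: 196 × 0.30 = 58.8, about 59. Left: 196 × 0.70 = 137.2, about 137.

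**4. Range.**
- Lower dropout (assumed): at 10%, 196 × 0.10 = 19.6 lost; at 20%, 196 × 0.20 = 39.2 lost.
- 30% dropout plus intermittent misses: suppose those who reach T3 also miss T1 or T2 independently with probability q per visit (assumed). Complete cases = 196 × 0.70 × (1 − q)². For q = 0.03, 0.05 and 0.10 this gives 129, 123 and 111, rounded down. The losses are then 67, 73 and 85 participants, or 34% to 43% of those randomised.

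**5. Measured values thrown away.** Suppose dropout builds as 10%, 20% and 30% by T1, T2 and T3 (assumed). Then 196 × 0.90 = 176.4 have T1, 196 × 0.80 = 156.8 have T2, and 137.2 have T3. Listwise deletion discards 176.4 − 137.2 = 39.2 observed T1 values and 156.8 − 137.2 = 19.6 observed T2 values. A model that uses partial data would draw on about 176 participants instead of about 137.

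**The case against.** The strongest answer is that the article never says that only participants with all four visits are analysed. It describes no complete-case set and does not list the modelled visits, and {20c} speaks of all participants' data. A mixed model in the same software would keep partial data, and an analysis plan that is not shown may specify one. This stands in part: the conflict arises under the method's default and is not a clash of two explicit statements. It does not remove the point. The article has a section on missing data and a named model, and as written the two cannot deliver the stated population for HbA1c.

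Four stronger readings are tempting and are not supported.

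- A reader might take 30% as the most that can be lost. It is a planning allowance; step 4 shows losses on either side.
- A reader might infer that the control arm is neglected and needs a new retention call. Controls keep standard therapy. The scheduling calls, the reminders 48 hours ahead, the discussion of results and the 50 EUR are described in {11c} and {18b} without restriction by arm. Only the moderator's extra prompt differs, and its effect is unknown.
- A reader might charge listwise deletion with a fall in power from about 81% (N = 157) to 76% (N = 137). Those are powers for a single-visit ANCOVA. If f = 0.229 held at each visit and the effect were averaged over T1 to T3, power at N = 137 would be about 79% to 95% for assumed correlations of 0.9 down to 0.3. For a comparison at T3 alone, about 137 values would exist under either method.
- A reader might size the bias by assuming that dropouts gain nothing, so that the completers' effect is inflated by 1/0.70. That ratio merely restates the assumption, and a mixed model does not target the diluted effect either.

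**Conclusion.** The point holds as a mismatch between the promised population and the named method. As normally run in SPSS, repeated measures ANCOVA would exclude about 59 of 196 participants at the planned 30% dropout, and no stated rule brings them back into the HbA1c analysis. This rests on two assumptions: that the default general linear model procedure is used, and that visits up to T3 enter the model. The documents do not fix the direction or size of any resulting bias, so none is claimed. The risk is real because allocation is open and encouragement to attend T3 differs by arm. It concerns the primary hypothesis and should be settled before outcome data are seen.

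**What to change.** In {20a}, replace repeated measures ANCOVA for HbA1c and the other continuous outcomes with a likelihood-based linear mixed model (SPSS MIXED). It should use all observed T1, T2 and T3 values of every randomised participant, with arm, visit, arm × visit and the baseline value as fixed effects. Visit-level multiple imputation before the planned analysis is an acceptable alternative.

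In {20c}, state that this is how missed visits are handled under intention to treat, and keep the nearest-neighbour rule for questionnaire items only. Add one sensitivity analysis that lets missing HbA1c values depart from missing at random, because a check for missing completely at random does not by itself protect the result. That analysis should also say how participants with no value after baseline are treated, since the mixed model gains nothing from them.

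If an analysis plan already specifies such a model, the two sections only need to say so. The cost is revised wording and slightly more analysis work, in the same software and with no new data.
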